#### 2.4 Inclusion Criteria

- (1) Receiving invasive mechanical ventilation for  $\geq 24$  hours.
- (2) Capable of initiating *spontaneous* breaths or *triggering* the ventilator to give a breath on ventilator modes commonly used in the ICU.
- (3) Fractional concentration of inspired oxygen ( $\text{FiO}_2$ )  $\leq 70\%$ .
- (4) Positive End-Expiratory pressure (PEEP)  $\leq 12$  cm  $\text{H}_2\text{O}$ .

#### 2.5 Exclusion Criteria

- (1) Brain death or expected brain death.
- (2) Evidence of myocardial ischemia in the 24 hour period before enrollment.
- (3) Received continuous invasive mechanical ventilation for  $\geq 2$  weeks.
- (4) Tracheostomy in situ at the time of screening.
- (5) Receiving a sedative infusion(s) for seizures or alcohol withdrawal.
- (6) Require escalating doses of sedative agents.
- (7) Receiving neuromuscular blockers or who have known quadriplegia, paraplegia or 4 limb weakness or paralysis preventing active mobilization.
- (8) Moribund (e.g., at imminent risk for death) or who have limitations of treatment.
- (9) Profound neurologic deficits (e.g., post cardiac or respiratory arrest, large intracranial stroke or bleed) or Glasgow Coma Scale (GCS)  $\leq 6$ .
- (10) Use of ventilator modes that automate SBT conduct.
- (11) Currently enrolled in a confounding study that includes a weaning protocol.
- (12) Previous enrollment in this trial.
- (13) Previous SBT or are already on T-piece, or CPAP alone (without PS), or PS  $\leq 8$  cm  $\text{H}_2\text{O}$  regardless of PEEP, or other 'SBT equivalent' settings immediately before randomization.
- (14) Previous extubation [planned, unplanned (e.g. self, accidental)] during the same ICU admission.

#### 2.6 Randomization and Consent

Research personnel (research coordinators and/or RTs) will identify, consent (where applicable) and enroll eligible patients from Monday to Friday during regular hours using a central randomization system, stratified by ICU with variable undisclosed block sizes. Patients will be randomized to a screening frequency (once vs. at least twice daily) AND an SBT technique (PS + PEEP vs. T-piece). The day of randomization will be considered study day one.

Given the minimal risk associated with the interventions being evaluated (screening frequency and SBT conduct) and the need to enroll patients as soon as possible after they initiate spontaneous breaths or trigger breaths, we will request ethics approval to use a hybrid consent model that prioritizes patient (with decision-making capacity) or SDM consent (when available) and permits deferred consent in their absence.

#### 2.7 Study Interventions

In the 'once daily screening arm', RTs will screen invasively ventilated patients between approximately 06:00 - 08:00 hours daily. In the 'at least twice daily' screening arm, patients will be screened at a minimum between approximately 06:00 - 08:00 hours and between 13:00 - 15:00 hours daily. If a

screening period is missed (inadvertently or due to an investigation or intervention (operation/procedure) necessitating absence from the ICU), it may be conducted later on the same day and ideally within 6 hours of the scheduled screening period. Additional screening trials in the 'at least twice daily' screening arm will be permitted at the discretion of clinicians caring for the patient. To standardize procedures, if a patient is randomized *before* 10:00 am, both screening strategies can be initiated on the day of randomization. For patients randomized *after* 10:00 am, only one screening assessment will be required on the first study day.

### 2.7.1 Screening for SBT Readiness

To pass a screening assessment and undergo an SBT, all of the following criteria must be met:

1. The patient must be capable of initiating spontaneous breaths on PS or PAV or triggering breaths on volume or pressure AC, volume or pressure SIMV  $\pm$  PS, PRVC, VS or APRV,
2. The ratio of partial pressure of oxygen to  $\text{FiO}_2$  ( $\text{PaO}_2/\text{FiO}_2$ )  $\geq 200$  mm Hg,
3.  $\text{RR} \leq 35$  breaths/min,
4.  $\text{PEEP} \leq 10$  cm  $\text{H}_2\text{O}$ ,
5.  $\text{HR} \leq 140$  beats/min,
6. The ratio of respiratory frequency to tidal volume ( $f/V_T$ )  $< 105$  breaths/min/L during a 2 minute assessment on CPAP of 0 cm  $\text{H}_2\text{O}$  (alternatively PS= 0 cm  $\text{H}_2\text{O}$  /PEEP = 0 cm  $\text{H}_2\text{O}$ ).

In selecting screening criteria, we avoided arbitrary criteria (no sedation, no vasopressors, hemoglobin above 100 g/L, and subjective assessments of level of consciousness) that may delay progression to an SBT. We included an objective measurement, the rapid shallow breathing index ( $f/V_T$ ), conducted on standardized settings [CPAP of 0 cm  $\text{H}_2\text{O}$  (alternatively PS= 0 cm  $\text{H}_2\text{O}$  /PEEP = 0 cm  $\text{H}_2\text{O}$ )] to determine progression to an SBT.

### 2.7.2 Conduct of Spontaneous Breathing Trials

After passing a screening assessment, COVID-19 negative patients will undergo an initial SBT according to treatment assignment (T-piece vs. PS + PEEP). COVID-19 positive patients will undergo an initial SBT with either [no support on the ventilator (i.e., PS=0 cm  $\text{H}_2\text{O}$  + PEEP=0 cm  $\text{H}_2\text{O}$  or CPAP = 0 cm  $\text{H}_2\text{O}$  vs. PS + PEEP]. All SBTs will be 30-120 minutes in duration [12,21,27]. SBTs will be conducted on T-piece (off ventilator with no CPAP/PEEP) or with PS  $> 0$  and  $\leq 8$  cm  $\text{H}_2\text{O}$  with PEEP  $> 0$  and  $\leq 5$  cm  $\text{H}_2\text{O}$ . Between SBT trials, patients will be returned to the mode of ventilation used before the SBT, unless criteria are met to remain on/return to a mode of support that assumes no spontaneous or triggered breaths. We will use standardized criteria to determine SBT failure in both arms [38].

SBT failure/Termination criteria is defined by the presence of any ONE of:

- a) a respiratory rate (RR)  $> 35$  breaths/min with signs of respiratory distress or an increase in RR  $\geq 20\%$  from baseline with signs of respiratory distress
- b) oxygen saturation of arterial blood ( $\text{SaO}_2$ ) or pulse oximetry  $< 90\%$ ;
- c) heart rate  $> 140$  beats/min with signs of respiratory distress or an increase in HR  $\geq 20\%$  from baseline with signs of respiratory distress;
- d) systolic blood pressure  $\geq 180$  or  $\leq 90$  mm Hg;
- e) the presence of somnolence, agitation, diaphoresis, or anxiety;
- f) requirement for the addition of or an increase in vasopressor or inotropic agent support; and
- g) chest pain or other limiting pain precluding further continuation.

After an unsuccessful SBT, patients will be returned to the ventilator settings used prior to the SBT. Ventilator settings will be adjusted to restore respiratory comfort, recognizing that some patients may meet criteria to go on a supported mode of ventilation without spontaneous or triggered breaths

### 2.7.3 Criteria to Suspend the Protocol and Return to a Controlled/Supported Mode of Ventilation

Patients should remain on a mode that permits spontaneous or triggered breaths between SBTs and at night. In all groups, patients will be permitted to *return to/remain on a supported mode of ventilation without spontaneous or triggered breaths* when any of the following criteria are met:

1. Surgery or invasive procedures requiring sedation and/or analgesia,
2. Respiratory distress as defined by:
  - a) sustained hypoxemia [pulse oximetry oxygen saturation ( $\text{SpO}_2$ )  $< 90\%$ ] with an  $\text{FiO}_2 > 60\%$  and PEEP  $> 10$  cm  $\text{H}_2\text{O}$  or hypercapnia with pH  $< 7.30$  OR clinical respiratory distress,

- b) Repeated episodes ( $\geq 3$  episodes within 1 hr) wherein an inspiratory pressure (drive pressure + PEEP on pressure modes or plateau pressure on volume modes) of 35 cm H2O or more is attained (despite suctioning, bronchodilation etc),
- 3. Hemodynamic instability despite fluid boluses and requirement for high dose vasopressors: norepinephrine  $> 15 \mu\text{g}/\text{min}$  ( $0.2 \mu\text{g}/\text{kg}/\text{min}$ ) or equivalent,
- 4. Suspected myocardial ischemia based on EKG and/or elevated Troponin I,
- 5. Neurologic deterioration with need to control PaCO2 (e.g., raised intracranial pressure) or central hypoventilation.
- 6. RR  $< 10$  breaths/min related to need for increased sedation,
- 7. PEEP  $\geq 13$  cm H2O,
- 8. FiO2  $\geq 71\%$ .

Patients meeting any of these criteria will be reassessed daily to identify the earliest time when they meet initial inclusion criteria and the screening and SBT protocols can be resumed as per initial treatment assignment. If patients can breathe spontaneously on PS or PAV, or trigger spontaneous breaths on volume or pressure AC, volume or pressure SIMV  $\pm$  PS, PRVC, VS, or APRV before 10:00 am, the allocated screening protocol can resume. However if, patients can not breathe spontaneously (PS or PAV) or trigger breaths (on volume or pressure AC, volume or pressure SIMV  $\pm$  PS, PRVC, VS, or APRV) until after 10:00 am, screening will be conducted only once daily in both treatment arms on the day of the return and will resume as per treatment allocation thereafter. Practices checklist assessments will not be mandatory while patients remain on a fully controlled mode.

**2.7.4 Extubation:** Patients who pass an SBT will be assessed for extubation using standardized criteria. Extubation should be performed as soon as possible after passing an SBT. To be extubated the following criteria [26,38] should be met

- 1) SpO2  $\geq 90\%$  or at baseline level in chronically hypoxemic patients on an FiO2  $\leq 40\%$  and PEEP  $\leq 5$  cm H2O,
- 2) a cough of sufficient strength to clear secretions and must not require suctioning more than every 2 hours,
- 3) patients should be hemodynamically stable [off vasopressors or on minimal levophed i.e.,  $\leq 7 \mu\text{g}/\text{min}$  ( $0.1 \mu\text{g}/\text{kg}/\text{min}$  or equivalent),
- 4) a level of consciousness sufficient to ensure airway protection and
- 5) a cuff leak is present. All of the above criteria (except #4 and 5) will also apply to patients who undergo trach mask trials and are disconnected.

### 2.7.5 Other Important Considerations (Noninvasive Ventilation, Reintubation and Tracheostomy)

**(i) Ventilator Titration:** Approaches to titration of ventilator settings, PEEP and FiO2 in both arms are detailed in Appendix 1. While on study protocol, RTs will assess and titrate ventilator settings, FiO2, and PEEP levels at least every 4 to 6 hours.

**(ii) Use of NIV after extubation:** We developed standardized criteria to guide the use of NIV after extubation. For NIV to be used after extubation, patients must have successfully completed an SBT and been extubated. In the FAST Trial, patients cannot be extubated directly to NIV to facilitate weaning as this technique obviates the need for an SBT. While our meta-analysis supports extubating patients [especially those with chronic obstructive pulmonary disease (COPD)] to NIV, our survey found that few clinicians have adopted this strategy in practice [25,39]. See Appendix 1.

**(iii) Criteria for reintubation:** All patients requiring reintubation after successful extubation will be ventilated according to usual practice and at the discretion of the clinical team. If patients are reintubated within 48 hours after extubation, they will be reassessed daily to identify the earliest time when they meet

study initial inclusion criteria once again so that screening for SBT readiness can resume. Patients will remain in the same group to which they were originally randomized. See Appendix 1.

**(iv) Criteria for Tracheostomy:** Patients who do not have a tracheostomy at study inclusion may receive a tracheostomy during their care, however, we will request in both groups that investigators, when possible, wait until at least day 10 before considering an elective tracheostomy [40,41]. To standardize care, we have developed criteria to guide performance of tracheostomy and weaning after a tracheostomy (Appendix 1).

**2.8 Challenges:** In this necessarily unblinded weaning trial, we will limit (i) *selection bias* by using central randomization with full allocation concealment, (ii) *identification bias* by having RTs lead screening and including an objective measure ( $f/V_T$ ) conducted on standardized settings in screening assessments, and (iii) *performance bias* by providing guidance statements on ventilator, PEEP and  $FiO_2$  titration; NIV use, reintubation, and tracheostomy). To enhance generalizability, we will permit SBTs of 30 -120 min duration.

**2.9 Duration of Follow Up:** In all 4 groups, we will collect daily data up to successful extubation, ICU discharge, ICU death, or until day 60 after randomization (deemed ventilator dependent) whichever comes first. All patients will be followed to hospital discharge.

## 2.10 Outcomes

**2.10.1 Primary Outcome:** Aligned with our survey results [24] and informed by discussions with our PFAC, the primary outcome will be the *time to successful extubation* – signalling timely and safe liberation from the ventilator. Successful extubation is defined as the time when unsupported, spontaneous breathing BEGAN and was sustained for  $\geq 48$  hours after extubation/disconnection in patients with tracheostomy [38].

**2.10.2 Secondary Outcomes:** We prioritize secondary outcomes that are patient-centred [42] and important to citizens including: [1] Time to first passing an SBT, [2] ICU mortality, [3] Hospital and 90 day mortality [31], [4] Total duration of mechanical ventilation (invasive and noninvasive), [5] ICU length of stay, [6] Hospital length of stay, [7] Use of NIV after extubation, [8] VAP, [9] adverse events, self-extubation, tracheostomy, reintubation, prolonged ventilation at d14 and d21, ICU readmission [32,33], [10] proportion receiving sedation/ analgesia/ antipsychotics at key time points or [11] screened positive for delirium at key time points, [12] HRQoL (EuroQoL EQ-5D) 6 months after randomization [34], [13] functional status 6 months after randomization using the FIM [35-37].

**2.11 Analytic Plan:** We will summarize baseline data using descriptive statistics [43]. All analyses will be performed adhering to the intention-to-treat principle.

**2.11.1 Primary Analysis:** Time-to event outcomes present special challenges because death is a competing risk and survivor only analyses are improper sub-groups. We will construct cumulative incidence curves to provide outcome estimates accounting for death for screening frequency and SBT technique. Cause-specific treatment effects will be depicted with hazard ratios (HR) (95% CI) from Cox models.

**2.11.2 Secondary Analysis:** We will report treatment effects in time to event analyses using HR and odds ratio (OR) with 95% CIs for binary outcomes and mean difference for continuous outcomes [43].

**2.11.3 Exploratory and Adjusted Analyses:** To assess the effect of age (continuous variable) by treatment interaction on the HR of time to successful extubation, we will construct a Cox regression model using a restricted cubic spline for age. Instead of arbitrarily assigning different levels for each age group, period, and cohort, a smoothing function or spline [collections of cubic polynomials joined smoothly at predefined number of points (knots)] will be created. The number of knots is expected to be between 3 and 5 but will be selected based on the sample size assuming the relationship with age will change gradually and smoothly. We will evaluate fitting using bootstrap techniques. As an extension of linear models, this technique allows for nonlinearities and interactions (between variables) that are more flexible than the linear contrasts traditionally used in regression models and is easier to depict and interpret [44]. In exploratory analyses, we will assess for an interaction between screening frequency and SBT technique. In adjusted analyses, we will consider variables (e.g., COPD, frailty score etc.) of potential prognostic importance.

**2.11.4 Interim Analyses:** Interim analyses for safety (adverse events) and efficacy (primary outcome) will be performed at 25%, 50% and 75% of accrual. Given the risks of stopping early for benefit, statistical significance will be declared using small p-values according to the O'Brien-Fleming boundaries for the primary outcome (time to successful extubation) and reintubation rate [45].

**2.11.5** In lieu of the emerging COVID-19 pandemic, we will enroll up to 250 additional critically ill patients who test positive for COVID-19 alongside the originally planned 760 (COVID-19 negative) patients. In this manner, we will be able to report on weaning and clinical outcomes in COVID-19 positive and COVID-19 negative patients combined and separately. The primary, secondary, exploratory, and adjusted analyses will report on 760 COVID-19 negative patients. We will also report the primary and secondary outcomes in COVID-19 positive patients alone and with both cohorts (COVID-19 positive and negative) combined.

**2.12 Sample Size Justification:** Most weaning trials report mean or median total duration of ventilation, weaning time, or ventilator free days which are confounded by pre-randomization duration of ventilator support, premature (unsuccessful) extubations, and weighting of deaths. Only 2 weaning trials, enrolling 144 and 92 patients invasively ventilated for  $\geq 24$  hours in mixed medical surgical ICUs, reported median time to successful extubation of 5 days [46] in the control groups, and 3 days [46] or 4 days [38] in the intervention groups. Similarly, a trial comparing two sedation minimization strategies in 430 patients invasively ventilated for  $> 48$  hours reported median times to successful extubation of 7 days in both strategies [47]. These estimates align with median weaning times reported in the control [range: 4.0-5.0 days] and intervention groups [range: 1.6-4.0 days] of other sedation and weaning trials and our pilot trials [11,16,48,49]. Our sample size estimates are entirely contained within these estimates.

**2.12.1 Minimal Clinically Important Difference:** In our pilot trials, some patients in both arms were recognized to be breathing spontaneously on a morning screen, passed an SBT, and were extubated - saving a full day of ventilation. In addition, some patients randomized to 'at least twice daily' screening passed an SBT in the afternoon and were extubated at least 3/4 of a day earlier. Reducing the time to successful extubation by even a part of a day has important implications for patients, hospitals, and our health care system. For patients, each day of invasive ventilation increases their exposure to harmful co-interventions (sedation), risk for developing VAP, discomfort, and distress. Since most ICUs operate at or near capacity with a fixed number of beds, saving a partial or full day of invasive ventilation would enable care to be provided to other patients and transfers from other care settings (Emergency Departments, recovery units, hospital wards, and referring hospitals) reducing wait times, adverse events (e.g., length of stay) and providing a more equitable and ethical distribution of limited ICU resources [50-52]. While underpowered, our pilot trial estimates suggest that at least a full day of ventilation may be saved.

**2.12.2 Sample Size Estimate:** To take into consideration deaths before successful extubation, we used cumulative incidence curves generated from our pilot trials and computed 3 mortality HRs per patient day [HR 2.9% (Release Trial) and HR 3.3% (SENIOR Trial) and HR 3.2% (combined)] to compute the sample size [27]. To demonstrate a reduction in time to successful extubation from a median of 5.0 days to 4.0 days [HR 1.25] [38,46] with 80% power and  $\alpha = 0.05$ , and allowing for 3 interim analyses, the proposed trial would require 760 patients. *A priori*, we do not expect an interaction since mechanistically and sequentially an interaction is very unlikely. Since the groups are orthogonal, the main effects (in the absence of interactions) will have the same power to detect the same size differences (see Sample Size Table below).

| Median time
(Once daily) | Median time (At Least
Twice daily) | Hazard
Ratio | Power      | Alpha       | N           |
|-----------------------------|---------------------------------------|-----------------|------------|-------------|-------------|
| 5.0 days                    | 4.2 days                              | HR 1.19         | 80%        | 0.05        | 1244        |
| 5.0 days                    | 4.1 days                              | HR 1.22         | 80%        | 0.05        | 960         |
| 5.0 days             | 4.0 days                       | HR 1.25  | 80% | 0.05 | *760 |
| 4.5 days                    | 3.4 days                              | HR 1.32         | 80%        | 0.05        | 472         |
| 4.0 days                    | 3.5 days                              | HR 1.14         | 80%        | 0.05        | 2064        |

**2.13 Timeline:** The trial will be conducted in 7 phases over 54 months: (i) start-up/recruitment (31 months), (ii) 6 month follow-up assessments (months 11 to 37), (iii) data cleaning (months 32-40), (iv) trial close out

(months 41-43), (v) trial analysis/manuscript preparation (months 44-48), (vi) follow-up outcomes close out (months 48-50), and (vii) follow-up analysis/manuscript preparation (months 51-54). We expect to recruit 2 patients per ICU per month. We allowed for variable REB approval times during start-up and for monthly recruitment to 'ramp up' (see Recruitment Table below). We plan to publish 3 manuscripts: (i) protocol and analytic plan (month 6), (ii) trial results (month 48), and (iii) HRQoL and functional status results (month 54).

| Study Month             | 1           | 2           | 3           | 4           | 5          | 6          | 7          | 8            | 9            | 10           | 11           | 12           |
|-------------------------|-------------|-------------|-------------|-------------|------------|------------|------------|--------------|--------------|--------------|--------------|--------------|
| Recruitment
No. ICUs | Start
up | Start
up | Start
up | Start
up | 2
[1]   | 2
[1]   | 4
[2]   | 6
[6]     | 10
[10]   | 14
[14]   | 18
[18]   | 20
[20]   |
| Study Month             | 13          | 14          | 15          | 16          | 17         | 18         | 19         | 20           | 21           | 22           | 23           | 24           |
| Recruitment
No. ICUs | 24
[20]  | 27
[20]  | 30
[20]  | 30
[20]  | 30
[20] | 35
[20] | 35
[20] | 35
[20]   | 40
[20]   | 40
[20]   | 40
[20]   | 40
[20]   |
| Study Month             | 25          | 26          | 27          | 28          | 29         | 30         | 31         | 32           | 33           | 34           | 35           | 36-37        |
| Recruitment
No. ICUs | 40
[20]  | 40
[20]  | 40
[20]  | 40
[20]  | 40
[20] | 40
[20] | 38
[30] | Follow
up | Follow
up | Follow
up | Follow
up | Follow
up |

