## 2.0 Research Approach and Methods

**2.1a) Primary Objectives:** The primary objectives of the FAST trial are to demonstrate the effect of:

- (i). The alternative screening strategies ('once' vs. 'at least twice' daily) on time to successful extubation.
- (ii). The alternative SBT techniques (T-piece vs. PS + PEEP) on time to successful extubation.

**2.1b) Secondary Objectives:** In secondary objectives, we will obtain estimates of the impact of the alternative screening and SBT techniques on clinically important outcomes including time to first passing an SBT, ICU mortality, hospital and 90 day mortality [31], total duration of mechanical ventilation, ICU and hospital length of stay, use of noninvasive ventilation (NIV) after extubation, VAP, adverse events, self-extubation, tracheostomy, reintubation, prolonged ventilation at day14 and 21, ICU readmission [32,33], proportion receiving sedation/ analgesia/ antipsychotics or screened positive for delirium at key time points, health related quality of life (HRQoL)(EuroQuol EQ-5D) and a functional status assessment [the Functional Independence Measure (FIM)] assessed 6 months after randomization [34-37].

**2.2 'A Priori' Hypotheses:** *A priori*, we expect that patients who are screened more frequently will have a shorter time to successful extubation regardless of the SBT technique used. We do not expect SBT technique alone to influence the time to successful extubation or successful extubation rate.

**2.3 Study Population:** We will include 760 COVID-19 negative and up to 250 COVID-19 positive critically ill adults [ $\geq 18$  years of age (USA) or  $\geq 16$  years of age (Canada) or admitted to an adult ICU] who are receiving invasive ventilation for at least 24 hours in 20 North American ICUs. Based on our pilot trials, we expect to recruit, on average, 1 out of every 5 patients screened by research personnel (1 in 5 for RELEASE; 1 in 5.3 for SENIOR) or 2.58 patients/ICU per month over a 31 month recruitment period. To be conservative, we expect to recruit 2 patients/ICU per month.

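### Total duration of mechanical ventilation (secondary outcome 4) has no stated start; if counted from intubation, pre-randomisation time adds avoidable noise, though no bias

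*Combined protocol and SAP*

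**What the plan says.** The objectives (2.1b) include "total duration of mechanical ventilation, ICU and hospital length of stay", and 2.10.2 repeats the first item as "Total duration of mechanical ventilation (invasive and noninvasive"). Neither place gives a start, and ICU and hospital stay have none either. The same list includes "prolonged ventilation at d14 and d21".

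Section 2.12 explains why results from earlier weaning trials are hard to use. They mostly report total duration of ventilation, weaning time or ventilator-free days, "which are confounded by pre-randomization duration of ventilator support, premature (unsuccessful) extubations, and weighting of deaths".

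Eligibility sets the possible range of earlier ventilation. Inclusion criterion 1 in 2.4 requires at least 24 hours, and exclusion criterion 3 in 2.5 removes patients with 2 weeks or more.

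Section 2.11.2 plans a mean difference for continuous outcomes. Section 2.11.3 gives COPD and frailty score as examples of adjustment variables and leaves the list open; prior ventilation is not named. Section 2.6 makes the day of randomisation study day one.

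**The concern.** The protocol criticises a measure partly because it carries time accrued before randomisation, then lists that measure as a secondary outcome without saying whether this time is counted. Elsewhere it names a randomisation clock explicitly: day 60 in 2.9, and the 6-month quality-of-life and function assessments in 2.10.2. The word 'total', read with 2.12, points to intubation. Two analysts could reasonably compute different values from the same data.

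Precision is at stake. Neither screening frequency nor SBT technique can change ventilation that has already happened. Including those days adds between-patient variance to an outcome on which the planned difference is small.

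**Working it through.** **1. The plan's own figure.** Inputs from 2.12.2: medians 5.0 and 4.0 days, HR 1.25, 80% power, alpha 0.05 (taken as two-sided), combined death hazard 3.2% per patient-day. Allocation is taken as 1:1 for each factor.

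- Events (Schoenfeld): 4 × (1.960 + 0.842)² / (ln 1.25)² = 631.
- Daily extubation hazards: ln 2/5 = 0.1386 and ln 2/4 = 0.1733.
- Probability of extubation before death: 0.1386/(0.1386 + 0.032) = 0.812 and 0.1733/(0.1733 + 0.032) = 0.844; mean 0.828.
- N = 631/0.828 = 762, against 760 stated.

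The 760 reproduces. It rests on time to successful extubation, so nothing below affects it.

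**2. Mean difference counted from randomisation.** The 1-day shift is stated for the primary outcome and is borrowed here for duration of ventilation. Times are exponential and deaths are ignored.

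- Means: 5/ln 2 = 7.21 and 4/ln 2 = 5.77 days; difference 1.44 days.
- Average variance, using SD = mean for an exponential: (7.21² + 5.77²)/2 = 42.7, so SD 6.53.
- Standard error with 380 per arm (760/2): 6.53 × √(2/380) = 0.474.
- Power: Φ(1.44/0.474 − 1.96) = Φ(1.08) = 86%.

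**3. The same difference counted from intubation.** Prior ventilation with SD s, taken as independent of later time, raises the variance to 42.7 + s². The 1.44-day difference does not move, because prior time has the same expectation in both arms. The documents give no s, so a range is shown. The top value is a uniform spread over the whole permitted window: (14 − 1)/√12 = 3.75.

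| Assumed SD of prior ventilation (days) | SD of outcome (days) | Share of variance from prior time | Power, 380 per arm | Total N for 80% power |
|---|---|---|---|---|
| 0 (from randomisation) | 6.53 | 0% | 86% | 644 |
| 1 | 6.61 | 2% | 85% | 660 |
| 2 | 6.83 | 9% | 83% | 704 |
| 3 | 7.19 | 17% | 79% | 780 |
| 3.75 | 7.53 | 25% | 75% | 856 |

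**4. Check as a time-to-event outcome.** Log-rank simulation with 380 per arm, death hazard 3.2% per day, follow-up cut at day 60 and 4,000 runs per setting:

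- From randomisation: power about 80%, HR 1.25.
- From intubation, prior SD 1.5 days: 77%, HR 1.24.
- From intubation, prior SD 2.6 days: 74%, HR 1.23.
- From intubation, prior time uniform over 1 to 14 days: 68%, HR 1.22.
- No treatment effect (20,000 runs, uniform prior time): mean HR 1.00 and upper-tail rejection 2.4% to 2.5% with either origin, against a nominal 2.5%.

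Both approaches show lost precision. Neither shows bias or inflated type I error.

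**The case against.** The intubation clock is an inference. 'Total' in 2.10.2 may simply mean invasive plus noninvasive time. Appendix 1 and the part of the protocol between 2.13 and 3.1.5 were not available, so a definition there cannot be excluded. This stands. What is certain is that the start is not stated in the objectives, the outcome list or the analytic plan.

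The protocol also acts on its own criticism by making time to successful extubation primary. Keeping a conventional measure as secondary is defensible, since the meta-analysis cited in 1.2 uses it. This stands as well: the measure can remain, but it need not be the analysed version.

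A reader might infer three stronger points that the documents do not support.

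- *That the comparison is confounded.* Section 2.12 uses that word, but prior ventilation is a baseline quantity that randomisation balances on average.
- *That up to 2 weeks of untreated time swamps a 1-day effect.* Two weeks is the ceiling for one patient; the loss depends on the SD across patients. A ratio would shrink, but 2.11.2 plans a mean difference. With an assumed 3 days of prior ventilation, 8 − 7 equals 5 − 4.
- *That the day-14 outcome is fixed by the entry rule.* With randomisation as study day one, days 14 and 21 most naturally mean study days. On that clock the day-14 risks are 0.5^(14/5) = 14.4% and 0.5^(14/4) = 8.8%, ratio 0.62. Even from intubation, with 3 prior days, they are 0.5^(11/5) = 21.8% and 0.5^(11/4) = 14.9%, ratio 0.68. The ratio comes close to 1 only for patients entering near the 2-week limit, and nothing shows that such entry is typical.

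**Conclusion.** The point holds as one of definition and precision. Outcome 4 has no stated time origin and, read with 2.12, appears to include ventilation before entry. If it does, power for the mean difference falls from about 86% to between 75% and 85%, a loss of about 1 to 11 percentage points. That range rests on exponential times, the primary outcome's medians, 380 per arm, no deaths, and assumed prior-ventilation SDs of 1 to 3.75 days. The expected mean difference and type I error do not change, and the primary analysis and sample size are untouched. Severity is minor, because only secondary outcomes are involved.

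**What to change.** - In 2.10.2, count duration of ventilation, ICU stay and hospital stay from randomisation.
- In 2.11.2, adjust these analyses for pre-randomisation ventilator days. Any gain beyond the change of origin depends on how strongly prior ventilation predicts later duration, which the documents do not show.
- Report total duration from intubation as a descriptive figure only.
- Write 'study day 14' and 'study day 21' for prolonged ventilation.

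The change of origin removes only the first of the three faults listed in 2.12, so the handling of deaths in outcome 4 should be stated in the same edit.

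The cost is wording plus one covariate already known from checking eligibility; no new data are needed. Comparison with earlier trials becomes slightly less direct, and the descriptive figure preserves it.
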